# Guided meditation as an adjunct to enhance postoperative recovery after cardiac surgery: study protocol for a prospective randomized controlled feasibility trial

**DOI:** 10.1186/s13063-018-3103-8

**Published:** 2019-01-11

**Keywords:** Meditation, Isha Kriya, Prehabilitation, Cardiac surgery, Postoperative cognitive decline, Delirium, Montreal Cognitive Assessment (MoCA), Depression, Anxiety, and Stress Scale (DASS-21), Pittsburgh Sleep Quality Index (PSQI), Patient-Reported Outcomes Measurement Information System (PROMIS) Surveys

## Abstract

**Background:**

Cardiac surgical procedures are associated with postoperative neurological complications such as cognitive decline and delirium, which can complicate recovery and impair quality of life. Perioperative depression and anxiety may be associated with increased mortality after cardiac surgeries. Surgical prehabilitation is an emerging concept that includes preoperative interventions to potentially reduce postoperative complications. While most current prehabilitation interventions focus on optimizing physical health, mind–body interventions are an area of growing interest. Preoperative mind–body interventions such as Isha Kriya meditation, may hold significant potential to improve postsurgical outcomes.

**Methods:**

This is a prospective, randomized controlled feasibility trial. A total of 40 adult patients undergoing cardiac surgery will be randomized to one of three study groups. Participants randomized to either of the two intervention groups will receive meditative intervention: (1) commencing two weeks before surgery; or (2) commencing only from the day after surgery. Meditative intervention will last for four weeks after the surgery in these groups. Participants in the third control group will receive the current standard of care with no meditative intervention. All participants will undergo assessments using neurocognitive, sleep, depression, anxiety, and pain questionnaires at various time points in the perioperative period. Blood samples will be collected at baseline, preoperatively, and postoperatively to assess for inflammatory biomarkers. The primary aim of this trial is to assess the feasibility of implementing a perioperative meditative intervention program. Other objectives include studying the effect of meditation on postoperative pain, sleep, psychological wellbeing, cognitive function, and delirium. These will be used to calculate effect size to design future studies.

**Discussion:**

This study serves as the first step towards understanding the feasibility of implementing a mind–body intervention as a prehabilitative intervention to improve postoperative surgical outcomes after cardiac surgery.

**Trial registration:**

Clinicaltrials.gov, NCT03198039. Registered on 23 June 2017.

**Electronic supplementary material:**

The online version of this article (10.1186/s13063-018-3103-8) contains supplementary material, which is available to authorized users.

## Background

Hospital admissions and surgeries have been increasing with time due to a shifting pattern of disease prevalence from infectious diseases to lifestyle disorders [1]. Cardiovascular diseases are increasingly seen in the elderly with various co-morbidities such as hypertension, diabetes, and renal impairment; they often require surgery [2]. Patients who undergo cardiac surgery can have significant pain, sleep impairment [3, 4], postoperative delirium (POD), and cognitive decline (POCD) [5], which can lead to increased length of hospital stay and increased healthcare expenses. Postoperative pain and sleep impairment can have a direct impact on postoperative delirium and cognitive recovery and the complications can be long lasting which can negatively impact the quality of life [6]. Evidence suggests that non-surgical preoperative patient factors such as psychological characteristics, personality traits, and preoperative cognitive impairment may also play a significant role in surgical recovery and patient satisfaction [7, 8]. Anxiety and depression in the perioperative period have been associated with increased mortality after cardiac surgery [9]. Thus, there is a definitive role for mind–body prehabilitative interventions to improve postoperative outcomes.

Surgical prehabilitation is an emerging concept that refers to interventions in the preoperative period aimed at improving postsurgical outcomes. These are pre-emptive strategies including physical therapies, pharmacological, and non-pharmacological measures to improve outcomes. In their review, Culley et al. mentioned that surgery can be compared to a fire and prehabilitation as a fire retardant [10]. Mind–body interventions include a wide range of practices and therapies that positively impact the mind’s influence on physical health [11]. Mind–body interventions have been shown to promote sleep and reduce postoperative delirium [10, 12, 13]. Integrative cardiac wellness programs can have a positive impact and can promote patient’s innate ability to heal [14].

In an expanded systematic review, it was reported that relaxation interventions and hypnosis could have a positive influence on psychological wellbeing [15]. Only two studies included in the expanded systematic review were of high quality [16, 17]. Most of the other studies did not have randomization or blinding of the outcome assessors, leading to inconclusive results. Lack of reporting pain scores was a significant limitation of the studies.

Another systematic review of randomized controlled trials examining relaxation for acute pain management similarly concluded that though there was “some weak evidence” to support the use of these therapies, the data were inconclusive, in part owing to methodological limitation [18]. The mind–body intervention was used only one day before surgery in most of the studies included in the meta-analysis. Another review provides evidence supporting the efficacy of mind–body interventions for depression, anxiety, and stress [19].

A recent study done by Kiran et al. explored the role of Rajyoga meditation, a certain type of meditation for the modulation of anxiety and serum cortisol in patients undergoing coronary artery bypass surgery. This study showed that the addition of meditation helped patients in coping with stress and they found a significant decline in anxiety levels in the postoperative period. They also found a favorable modulation of serum cortisol levels with the meditation [12]. The above studies demonstrate that breathing and meditative techniques have a biological plausibility to favorably impact outcomes. They have been shown to have established use in non-surgical chronic disease states such as fibromyalgia, cancer, hypertension, and psoriasis [20].

Finding a meditation technique that has the optimal components and that is easy enough to ensure compliance is a challenge. Meditation encompasses a family of different systems and practices including yoga meditation, mantra meditation, tai chi, mindfulness meditation, etc. Isha Kriya (IK) is a form of guided meditation that involves thought, focus, and mindful slow breathing. This regimen was chosen because it excels in simplicity and is suitable to introduce meditation to beginners.

Regarding timing and duration of application of these prehabilitative measures, research groups have studied interventions of durations in the range of 1–30 days before surgery [21, 22]. In earlier studies that examined psychosocial support, a duration as short as one day before surgery was used for intervention [18]. In preoperative exercise therapies, a 3–4-week period was used. Although optimal duration is not clearly defined, based on the current scheduling practices for surgery, two weeks is a reasonable preoperative timeframe to investigate. This randomized, controlled pilot trial will examine the feasibility of implementing a prehabilitative meditation program in the perioperative period.

## Methods / design

### Study registration

This study protocol was approved by the Committee on Clinical Investigations Institutional Review Board (IRB) at Beth Israel Deaconess Medical Center (Protocol 2017P000239). This trial was registered with the U.S. National Institutes of Health on clinicaltrials.gov with the trial identification number NCT03198039 on 23 June 2017. The trial is currently ongoing and recruiting.

### Study design

This study is a prospective, randomized, controlled, assessor blinded, single-center trial with three arms, including two experimental arms and one control arm. The study population will include adult patients undergoing coronary artery bypass grafting (CABG), valve surgeries, and/or aortic surgery at Beth Israel Deaconess Medical Center, a tertiary care hospital. Informed consent will be obtained before initiation of study procedures. Further, all trial conduct and reporting will be in accordance with components as described in the SPIRIT (Standard Protocol Items: Recommendations for Interventional Trials) checklist [23, 24].

### Aims and objectives

We hypothesized that it is feasible to implement a meditation program aimed at improving outcomes in the adult cardiac surgical population. The primary aim of this pilot study is to assess the feasibility of implementing a meditation program in the preoperative period, which will be measured in terms of adherence of the participants to the meditative regimen. Our study will further explore whether a perioperative meditation regimen can result in improvement in postoperative outcomes including pain, sleep, psychological wellbeing, cognitive function, and delirium. Given the pilot nature of the proposed trial, all secondary outcomes will be considered hypothesis generating only.

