### Recruitment and randomization

Individuals will be identified from perioperative surgical consult lists and cardiac surgery clinic visit schedules. If a candidate is eligible for enrollment, he or she will be approached by a member of the research team to discuss the study in detail. Written informed consent will be obtained before initiation of any study procedures.

After obtaining consent, enrolled participants will be randomly assigned to one of three groups using block randomization in a 1:1:1 allocation. REDCap will be utilized to implement the randomization schema while maintaining the blind. REDCap is a secure software designed for rapid data capture tools using metadata table referenced by presentation-level operational modules [24]. Patients will be randomized to one of the following groups:Group 1: Patients are asked to meditate twice daily, starting from least two weeks before surgery, up until four weeks after surgery;Group 2: Patients are asked to meditate twice daily from the day after surgery until four weeks after surgery;Group 3: Patients in the control group will undergo surgery and subsequent hospital stay according to the current standard of care, which does not include meditation.

Patients who are actively meditating previously and are willing to participate in the study will be asked to refrain from meditating during the study period if they are randomized to the control group. They will be required to follow the IK meditation schedule during the period of study participation if they are randomized to one of the intervention groups.

The inclusion of a control group will allow for quantification of the natural history of surgery and postoperative complications. Further, we are utilizing two interventional groups to assess whether a prehabilitative strategy results in differences as compared to a mitigation strategy. Two intervention groups will also help us determine the optimal duration of intervention and the possible impact of duration on compliance and other secondary outcomes.

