### Study outcomes

The primary outcome of the study is to assess the feasibility of implementing a meditation routine in the perioperative period. This will be evaluated using the adherence data from patients’ meditation diary. Secondary exploratory outcomes include effects of the intervention on pain, sleep, psychological wellbeing, cognitive function, and delirium. A number of tools, including pain scores, questionnaires for cognition and delirium assessment, depression and anxiety questionnaire, sleep questionnaires, total opioid consumption and supplemental analgesic requirements in the first 48 h postoperatively, Intensive Care Unit (ICU) stay, and hospital length of stay, will be used to measure the secondary outcomes. In addition, we will also evaluate inflammatory biomarkers measured in plasma. All secondary outcomes will be considered hypothesis generating and interpreted as such (Fig. 2).

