### Meditation adherence

To assess study feasibility, we will evaluate adherence to the study protocol. Patients in the meditation groups will be provided with meditation diaries, where they will be asked to record their daily meditation sessions. Adherence to the meditation schedule will be assessed by calculating the total number of meditation sessions completed divided by the total number of sessions required as per protocol.

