### Statistical analysis

In this feasibility study, a convenience sample of 30 participants (10 per group) will be enrolled to assess feasibility. While we expect it to be very rare, it is possible that some individuals may be determined ineligible after signing consent (because of their baseline MoCA or DASS-21 depression scores). Therefore, we plan to enroll enough patients to obtain data from 30 randomized participants. We estimate that approximately 40 patients may be enrolled to account for dropouts, loss of follow-up, and to achieve this sample size of 30. No a priori power calculation was performed.

Since the primary outcome of the study assesses the overall feasibility of conducting the trial, our descriptive study will record the proportion of patients eligible who meet inclusion without exclusion criteria and decide to participate. The statistics for overall protocol adherence to the intervention will be recorded by reporting the total number of sessions completed out of that required per protocol. We will also assess the total number of questionnaires completed out of the total required.

Descriptive statistics of data will be performed. Categorical data will be reported as proportions and assessed with the use of a chi-square or Fisher’s exact test. Continuous data will be reported as means ± standard deviations or median (quartile 1 and quartile 3) depending on distribution and assessed using analysis of variance (ANOVA). We estimate that with a small sample size it may not be acceptable to assume normality and may be appropriate to use a non-parametric equivalent such as Kruskal–Wallis test when appropriate. A trajectory analysis will be performed to assess changes in the presence of delirium or changes in cognitive function over time. Since the secondary outcomes are exploratory in nature, all tests will be two-sided, with *p* values < 0.05 considered statistically significant. Data will be analyzed using SAS 9.4 (SAS Institute Inc., Cary, NC, USA) or later. Our primary analysis will be conducted using the intention-to-treat principle. All trial reporting will adhere to the Standard Protocol Items: Recommendations for Interventional Trials (SPIRIT; Additional file 1: Table S1).

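### The primary aim is worded as preoperative in one section and perioperative in others, and the undivided adherence ratio can show neither preoperative adherence nor an effect of duration

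*Protocol article*

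**What the plan says.** All references are to the protocol article.

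**The aim.** Aims and objectives says the primary aim is to "assess the feasibility of implementing a meditation program in the preoperative period, which will be measured in terms of adherence of the participants". The Abstract (Methods) says: "The primary aim of this trial is to assess the feasibility of implementing a perioperative meditative intervention program". Study outcomes says: "The primary outcome of the study is to assess the feasibility of implementing a meditation routine in the perioperative period".

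**The measure.** Meditation adherence obtains adherence from the patients' diaries by "calculating the total number of meditation sessions completed divided by the total number of sessions required as per protocol". Statistical analysis repeats that "overall protocol adherence to the intervention will be recorded by reporting the total number of sessions completed out of that required per protocol". Neither section divides the count at surgery.

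**The schedules.** Under Recruitment and randomization, Group 1 meditates twice daily before surgery and for four weeks after it. Group 2 meditates twice daily for the four postoperative weeks only, and Study intervention asks it not to meditate before surgery beyond one practice session. Group 1's start is described as "commencing two weeks before surgery" in the Abstract and as "starting from least two weeks before surgery" in Recruitment and randomization.

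**The use of two groups.** Recruitment and randomization states: "Two intervention groups will also help us determine the optimal duration of intervention and the possible impact of duration on compliance". Future direction, in the Discussion, again expects the comparison of the two groups to indicate the best timeframe and duration.

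**The concern.** Only Group 1 has a preoperative phase, and that phase is what makes the programme prehabilitation. If the aim is read as Aims and objectives words it, the result that answers it is Group 1's adherence before surgery. The defined ratio mixes those sessions with a larger number of postoperative ones and cannot be unmixed afterwards. Future direction makes reasonable compliance the sign of feasibility and the basis for a larger study. That decision could rest on a figure that looks acceptable although few patients meditated before surgery, or on one that looks poor although the preoperative part went well.

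The second problem is the duration claim. Group 1 differs from Group 2 both in when meditation happens (before and after surgery versus after only) and in how long it lasts (at least six weeks versus four). No arm changes length while holding timing fixed. A difference in overall adherence, or in any outcome, therefore cannot be assigned to duration.

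**Working it through.** The article states no session count, adherence rate or threshold, so there is no figure of its own to reproduce.

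**Inputs from the article.** Two sessions a day; a preoperative lead of 14 days (the minimum); four postoperative weeks, taken as 28 days; 10 participants per group. The exact first and last day could move the counts by one or two sessions.

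**Assumed.** All adherence rates, since the article gives none. Let *a* be adherence before surgery and *b* adherence after it.

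**Required sessions**
- Before surgery, Group 1: 14 × 2 = 28
- After surgery, each group: 28 × 2 = 56
- Group 1 in total: 28 + 56 = 84; Group 2 in total: 56
- Preoperative share of Group 1's requirement: 28/84 = 1/3

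**What a Group 1 ratio reveals about the preoperative phase.** The ratio is (28*a* + 56*b*)/84. A value of 70% means 0.70 × 84 = 58.8 sessions.
- If *b* = 100%, then *a* = (58.8 − 56)/28 = 10%.
- If *a* = 100%, then *b* = (58.8 − 28)/56 = 55%.

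So 70% is compatible with any preoperative adherence from 10% to 100%. With *a* = 0 and *b* = 100%, the ratio is 56/84 = 67%.

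**What comparing the groups' overall ratios reveals.** Suppose both groups have the same postoperative adherence *b*. Group 2's ratio is then *b*, and the difference is (28*a* + 56*b*)/84 − *b* = (*a* − *b*)/3.

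| Assumed *a* / *b* | Group 1 | Group 2 | Difference |
|---|---|---|---|
| 90% / 60% | 70% | 60% | +10 points |
| 70% / 70% | 70% | 70% | 0 |
| 50% / 80% | 70% | 80% | −10 points |

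Group 1 shows 70% in every row, while preoperative adherence runs from 50% to 90%. Restricted to the shared postoperative weeks, the difference is zero in every row.

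**Effect of the two start descriptions.** For a patient with 28 days between enrolment and surgery, a start two weeks before surgery requires 28 + 56 = 84 sessions, with a preoperative share of 33%. A start at enrolment requires 56 + 56 = 112, with a share of 50%. At a 42-day lead the share would be 84/140 = 60%. The weight of the preoperative phase in the ratio thus depends on which description applies and on the wait.

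**The case against.** The strongest reply is that preoperative is the outlier. The Abstract and Study outcomes say perioperative, the Background and Ethics and dissemination sections place the programme in the perioperative period, and the sentence following the aim in Aims and objectives itself speaks of a perioperative regimen. For a perioperative aim, total completed over total required is a fair overall summary. This stands in part. A reader might infer that the measure simply fails the primary aim, but the documents do not support that without choosing the minority wording. They do show one primary aim stated in two ways, with a measure that suits only one of them.

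Other strong readings also go too far:
- **Pooling over both arms.** A reader might sum sessions across Groups 1 and 2, which would cut the preoperative share to 28/140 = 20%. The article does not say whether the ratio is per participant, per group or overall, so the working above stays within Group 1.
- **A false difference.** A gap of 70% versus 60% would be a true difference in adherence to each group's assigned regimen. It misleads only when read as an effect of duration, and it may be zero or negative.
- **Home versus hospital.** The postoperative phase runs four weeks and no length of stay is given, so the contrast is before versus after surgery and nothing narrower.
- **An undefined ratio.** A varying lead still allows the requirement to be computed for each participant from the start and surgery dates, once the start rule is settled.

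It can also be said that the adherence ratio is not the only feasibility measure (participation and questionnaire completion are reported too), that no between-group test of adherence is specified, and that an analysis plan not shown might add a split by phase. All fair. But the wording of the aim, the undivided ratio and the duration claims are stated in this article, and the other feasibility measures say nothing about preoperative meditation.

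**Conclusion.** The concern holds in a limited form. The primary aim is worded inconsistently, and the stated adherence ratio cannot identify preoperative adherence even within Group 1: at a 14-day lead, 70% overall fits 10% to 100% before surgery, and 67% is reachable with no preoperative sessions. This follows from the session counts and not from any assumed rate.

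Separately, the two intervention groups cannot deliver an optimal duration or an impact of duration on compliance, because timing and length change together. The size of the resulting gap in overall ratios, one third of (pre minus post), assumes a 14-day lead and equal postoperative adherence. The examples of +10, 0 and −10 points rest on assumed rates, and the documents do not indicate which direction is likelier.

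The fault lies in wording and in the defined summary. Randomisation and data collection are not affected.

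**What to change.** 1. Use one wording of the primary aim in the Abstract, Aims and objectives, and Study outcomes.
2. Compute adherence for each participant and separately for the preoperative and postoperative phases, then summarise over participants.
3. Report Group 1's preoperative adherence as a feasibility result in its own right.
4. Compare Groups 1 and 2 on adherence only over the four postoperative weeks they share.
5. Reconcile the two descriptions of Group 1's start so that the number of required sessions has one definition.
6. In Recruitment and randomization and in Future direction, replace the optimal-duration claims with the effect of adding a preoperative phase, which is what the randomised contrast estimates.

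The cost is protocol wording and analysis only, since the diaries already ask for daily sessions. The price in precision is that the preoperative result rests on about 10 people, so its interval will be wide and should be shown.
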